## Abstract

**Introduction::**

A substantial number of the world's population appears to end with moderate to severe long-term disability after stroke. Persistent uncontrolled stroke risk factor leads to unpredicted recurrent stroke event. The increasing prevalence of stroke across ages in Malaysia has led to the adaptation of medication therapy adherence clinic (MTAC) framework. The stroke care unit has limited patient education resources especially for patients with medication understanding and use self-efficacy. Nevertheless, only a handful of studies have probed into the effectiveness of video narrative at stroke care centers.

**Method::**

This is a behavioral randomized controlled trial of patient education intervention with video narratives for patients with stroke lacking medication understanding and use self-efficacy. The study will recruit up to 200 eligible stroke patients at the neurology tertiary outpatient clinic, whereby they will be requested to return for follow-up approximately 3 months once for up to 12 months. Consenting patients will be randomized to either standard patient education care or intervention with video narratives. The researchers will ensure control of potential confounding factors, as well as unbiased treatment review with prescribed medications only obtained onsite.

**Results::**

The primary analysis outcomes will reflect the variances in medication understanding and use self-efficacy scores, as well as the associated factors, such as retention of knowledge, belief and perception changes, whereas stroke risk factor control, for example, self-monitoring and quality of life, will be the secondary outcomes.

**Discussion and conclusion::**

The study should be able to determine if video narrative can induce a positive behavioral change towards stroke risk factor control via enhanced medication understanding and use self-efficacy. This intervention is innovative as it combines health belief, motivation, and role model concept to trigger self-efficacy in maintaining healthy behaviors and better disease management.

**Trial registration::**

ACTRN (12618000174280).

## Introduction

1

Stroke has been an enormous burden of disease at the global scale with upper-middle-income countries recording the highest prevalence, followed by lower-middle-income and high-income nations, as reported by the global statistics in 2012.^[1,2]^ A substantial number of the population ends with moderate to severe long-term disability after stroke.^[3]^ Up to a quarter of people who experience a transient ischemic attack (TIA) or stroke will proceed to recurrent stroke within a few weeks or months.^[4]^ An alarming morbidity rate due to stroke could paralyze the economic growth caused by incurring treatment expenses and loss of workforce.^[5]^ Modifiable recurrent stroke risk factors (e.g., hypertension, diabetes, and hyperlipidemia) and non-modifiable risk factors, such as sex, age, and familial history, are added-on with barriers to adherence to medication, which could cause a substantial loss in terms of money, time, and effort of various stakeholders.^[6–9]^ Besides, a recent study associated adherence to recurrent stroke preventative medication with reduced stroke occurrence.^[10]^

An estimate of 40,000 acute stroke cases are recorded yearly in Malaysia, and about 23% of hospitalization cases referred to patients with a history of recurrent stroke.^[11]^ Approximately, ischemic incidence have been reported to increase annually by 29.5%, while almost 18.7% for hemorrhagic stroke.^[12]^ In total, 33% from acute strokes end with moderate to severe disability. Mortality and morbidity rates of stroke have remained high due to the aging of the population.^[11]^ Hence, stroke recurrence initiatives seem to focus on combatting modifiable risk factors adapted via behavioral interventions.^[13,14]^ While neurologists prescribe preventative stroke medications, a critical component of effective modifiable stroke risk factor control rests with the individual.

The increasing prevalence of stroke across ages in Malaysia have led to the adaptation of medication therapy adherence clinic (MTAC) framework to assist patient care after being discharged from outpatient clinics.^[15]^ Patient education, as a construct of MTAC, addresses modifiable individual behavioral factors identified during clinic appointments. However, limited resources are at grasp regarding the type of intervention that may enhance medication understanding and use self-efficacy so as to promote medication adherence, especially for diseases with various underlying comorbidities, such as stroke.

A highly activated individual takes the effort to acquire disease-specific knowledge and self-efficacy, which lead to engagement in positive health behavior.^[16–18]^ Self-determination theory developed by Deci and Ryan^[19,20]^ explains that without external influences, there is a link between human motivation and personality characteristics with basic needs of satisfaction among patients. They have classified self-motivation into; intrinsic and extrinsic motivation. Intrinsic motivation involves the person engaging in a behavior as he or she finds the activity enjoyable, whereas extrinsic motivation occurs when the person is motivated to modify behavior to earn a reward or to avoid negative consequences.^[19,21]^ Hence, if the person is highly motivated, adhering to a specific medication regime would be a simple routine, otherwise it would be a burden that can affect one's quality of life.

Information-Motivation-Behavior (IMB) is a notable health behavior change framework applicable to patient education intervention.^[22,23]^ Adaptation of IMB model in patient education delivered via information technology, audio-visual, and personalized counseling reported significant behavioral changes.^[24–26]^ The information provides knowledge about risk factors and types of behavior or barriers towards adherence. Motivation is comprised of personal attitude, belief, and perception towards activation of the individual response, while behavioral skills are specific learning skills that enable positive behavior modification. On the other hand, self-efficacy influences the patient's confidence towards the final execution of an action concerning healthy lifestyle and medication management.^[22,27]^

Within the context of IMB, the foundation of information developed using health belief model (HBM) constructs would deliver a system that enhances understanding and self-efficacy of the patient towards better medication management.^[28,29]^ HBM suggests that individuals protect their health depending on their belief of susceptibility to a disease condition, that the occurrence of their disease condition would have an impact on their quality of life. With that aim, they have options for actions to avoid their perceived disease condition. Additionally, HBM suggests that individuals consider benefits of taking the planned action which outweighs their costs.^[30,31]^ Therefore, patient education intervention should adapt behavioral theories and framework for further exploration of disease risk factor control.

With IMB and HBM to be adopted as the conceptual frameworks, the study is projected to evaluate the impact of patient education on medication understanding and use self-efficacy delivered via video narrative. Video narrative is a useful tool that provides knowledge, improves confidence, and promotes self-learning among patients with various diseases.^[32,33]^ Narratives, as personal stories from comrades or professionals, are seen as motivator, persuader or a role model for other patients to react to their behavior.^[34]^ It can also overcome resistance and facilitate information processing.^[35]^ Thus, a doctor's narrative would be a source of a genuine informant supplementing a patient's story that is believed to strengthen motivation towards behavioral changes so as to minimize the detrimental psychological effects of stroke.

Based on prior studies, stroke risk factors were sequenced in descending order starting with the most prevalent risk factor; hypertension, diabetes mellitus, hyperlipidemia, ischemic heart disease, and history of a previous stroke; thus demanding the need for focused efforts to reduce recurrent stroke prevalence.^[36,37]^ To the researchers’ knowledge, various studies have faced considerable challenges to motivate stroke patients due to their varied perspectives regarding stroke severity and medication management. Therefore, this study hypothesizes that narratives developed on behavioral constructs, framework, and experiences of doctors and patients possess the ability to generate substantial expected outcomes. Thus, the study will disclose the specific challenges of medication management among recurrent stroke patients for whom the planned intervention would be most beneficial.

## Materials and methods

2

### Study design and aim

2.1

This is a single-blind, randomized controlled, parallel group, longitudinal, and exploratory trial in which patients with risk of recurrent stroke will receive either a video narrative and standard care or standard care alone. This study is due to start in the month of May 2018. The study outcomes are assessed as follows; at baseline: T0, 3 months: T1, 6 months: T2, 9 months: T3, and 12 months: T4, as outpatient follow-up. The design and the conduct of the study conform to the revised Consolidated Standards of Reporting (CONSORT) guidelines^[38]^ and adheres to Standard Protocol Items: Recommendations for Interventional Trials (SPIRIT)^[39]^ Approvals have been granted from the Malaysian Medical Research and Ethics Committee—MREC (NMRR ID-15-851-24737) and the Monash University Human Research Ethics Committee—MUHREC (ID 9640), while the study is registered with the Australian New Zealand Clinical Trials Registry—ANZCTR (ACTRN12618000174280) with Universal Trial Number (UTN) U1111-1201-3955. The research ethics committee and trial registry are notified if there are updates or protocol amendments. The study will be administered at the Neurology Department of Hospital Kuala Lumpur (HKL) in partnership with Jeffrey Cheah School of Medicine and Health Sciences, Monash University Malaysia.

The primary aim of the study is to determine if integrating a video narrative of a doctor and a patient into the standard patient education and counseling procedure will improve medication understanding and use self-efficacy, in comparison to the current standard patient education and counseling procedure. Here, the impact of reinforcement (e.g., repetition after 3 months’ interval at T1 and T2) will also be determined. Next, the secondary aim of this study is to explore the relationship between medication self-management and stroke risk factor control, as well as its effect on the quality of life among the stroke patients. The study achieves an endpoint if stroke recurs.

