### Sample size

2.3

A power analysis was carried out for an independent *t* test using the G∗Power version 3 to determine a sufficient sample size using an alpha of 0.05 and a power of 0.80.^[40]^ The estimation involved a medium effect size (*w* = 0.4) based on an average of effect sizes from similar recent studies associated to patient education in stroke, IMB, HBM, video narrative, and self-efficacy.^[25,41–43]^ However, sample size calculation according to stratification of stroke risk factors is not feasible because this is a disease with various underlying comorbidities and treatment heterogeneity. Thus, the desired sample size is 200 (100 each in intervention and control groups) are needed. With an estimated 15% attrition rate, 115 in each group will be recruited, thus yielding a target total sample size of 230.

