### Randomization

2.4

Randomization will be performed by using blocks of varying lengths, between 2, 4, and 6 in opaque envelopes to avoid bias. The order of the blocks and the allocations within each block will also be randomized. Assigning of patients to one of two study arms will take place after the baseline screening.The standard care (control group); based on MTAC framework will receive an appropriate referral for rehabilitation, nutrition counseling, and speech therapy from the neurology department. Aside from treatment review and advice, the department also provides short message service (SMS) reminders of next appointments. Pamphlets regarding common patient education information about stroke, and its preventative treatment, as well as a self-monitoring calendar, will be distributed. The information developed according to HBM constructs and MTAC guidelines is about stroke symptoms, preventative treatment adherence advice, and medication management. The patients will be provided with a general helpline in case of any inquiry pertaining to their treatment.The intervention group, that will receive standard care procedures, printed materials, reminders, and helpline similar to those in the control group, will also obtain a short face-to-face video narrative of a doctor and a patient's reflection about stroke.

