### Study procedures

3.1

With the supervision of a research neurologist, patient screening and randomization will be carried out by a clinic staff nurse who is not involved in this research. Patients will then complete their baseline assessments at the outpatient Neurology clinic. The neurologists will be blinded after the assignment. They will be advised to not to prompt patients regarding reception of intervention. One of the researcher ([name]) who is a pharmacist and a clinical educator, will conduct the baseline assessment. Patients randomized into the intervention arm will be displayed the video immediately after their clinic visit. All patients, regardless of study arm, will receive appropriate standard stroke treatment and medication management. At each consequent visit, the researcher will assess the level of medication understanding and use self-efficacy, while evaluation of stroke risk blood parameters will be done by the staff nurse at the clinic. The researcher will send reminder calls 3 days in advance to promote retention. At each clinic visit, both groups will receive MTAC standard care reminders to encourage self-monitoring, to modify lifestyle, to follow-up clinic appointments, and to enquire regarding their medications. Patients who miss their visits, move too far away, are referred to other outpatient clinics, and those who fail to respond up to 4 times of reminders will be noted as lost to follow-up and eventually withdrawn from the study. Also, if there is a need of unblinding due to the intervention's effect, the patient's allocation will be revealed to their neurologist and that patient is withdrawn from the study. These effects will be recorded and reported in the data analysis.

At each session, the patients will meet the neurologist first for their follow-up treatment review, and next, have further check on self-monitoring practice and lifestyle changes. The clinic staff nurse will assess their blood pressure and other appropriate blood parameters. After that, the clinic staff nurse will guide the patients into a quiet room, where the researcher will meet them individually for the outcome assessment or video viewing. The patients will view the video at baseline: T0, 3rd month: T1 and 6th month: T2 immediately after outcome measure assessment (Fig. 1).

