### Primary outcome measure

4.1

The primary outcome measure assessed at T0, T1, T2, T3, and T4 refers to medication understanding and use self-efficacy (MUSE).^[48]^ The study will observe the stage of medication usage behavior changes for each stroke preventative medication. MUSE with a scoring scale from 0 until 32 will be used to efficiently measure confidence in the understanding of individual's perceived ability using and adhering to the prescribed medicines, which differs from other medication-specific self-efficacy measures. Both the scales; learning and taking medication, have good internal consistency (Cronbach's alpha of 0.77 and 0.68) with acceptable construct validity and predictive validity. This scale has also been validated in the Malay language version.^[49]^

Knowledge and belief of the disease, as well as its preventative medication, have been associated with medication understanding and use self-efficacy. Therefore, the primary measures assessed at T0, T2, and T4 will also consist of validated Stroke knowledge test (SKT)^[50–52]^ and Brief illness perception questionnaire (BIPQ),^[53–55]^ whereby both have acceptable validity and reliability properties and available in the Malay language version. On top of that, this study will only adapt the BMQ specific Likert scale of the belief about medicine questionnaire^[56]^ so as to hinder redundancy and patient loading. This scale will be translated and validated in Malay language in a separate study. The SKT contains 20 questions with a scoring range of 0 to 20 regarding general information on stroke, such as pathophysiology, signs and symptoms, risk factors, and treatment methods and BIPQ, on the other hand uses a 0 to 10 scoring range of Likert-type scales for the general perception of one's illness. SKT measures differences in knowledge retention between groups whereby higher scores indicate better knowledge retention. BIPQ high scores reflect vulnerable thoughts of threatened attitudes about their disease, which will correlate to the impact of the intervention. Meanwhile, the BMQ specific is comprised of 2 scales; belief about the need of preventative medication (Necessity scale), and concerns about the potential adverse effect of the medication (Concerns scale). Higher scores indicate stronger beliefs about medicine usage.

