### Statistical analysis

4.3

Data entry will be done independently by a clinic staff nurse and verified by another. Hardcopies of data collection forms and outcome measures will be kept in a locked safe, whereas softcopies are to be deposited at the repository center (Lab Archives), both at Monash University in Malaysia. Only the principal investigators ([name]), ([name]), and ([name]) have access to the interim results and makes the final decision to terminate the trial. The study team ensures that patients’ identity and personal information are coded to maintain confidentiality. In addition, ([name]) and the biostatistician ([name]), who will also be blinded, will conduct the statistical analysis by using International Business Machines Statistical Package for the Social Sciences (IBM SPSS; IBM Corp. Released 2013. IBM SPSS Statistics for Windows, Version 22.0. Armonk, NY) (v.22). The initial analysis will consist of descriptive statistics on demographic data, such as frequency distributions. Meanwhile the mean differences in primary and secondary outcomes are compared by using *t* tests or equivalent statistical method, whereas categorical outcomes are matched using chi square test. *P* values <.05 are considered statistically significant. Generalized mixed model analysis is adapted to investigate the variances between groups over time for all outcomes evaluated at the allocated time. Furthermore, the association between medication understanding and use self-efficacy, stroke knowledge, illness perception scores, as well as engagement in self-monitoring and clinic appointment attendance will be tested, as they seem to be critical indicators of behavioral changes. Multivariable analysis will be employed to examine the influence of the video narratives on stroke risk factor control and their covariates.^[61]^ Multiple imputation will be adapted to handle missing data if it occurs. In addition, withdrawn patients’ feedback about the intervention will be analyzed.

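### The stated aim of determining the impact of repeat viewing cannot be met from T2 on without an unstated assumption about how the first viewing's effect evolves

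*Protocol article*

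**What the plan says.** All references are to the protocol article.

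- **Aim.** The primary-aim paragraph of section 2.1 goes beyond the video-versus-standard-care question. A sentence beginning "Here, the impact of reinforcement (e.g., repetition after 3" places the repeats at T1 and T2 and says that their impact will be determined.
- **Arms.** Section 2.1 says that patients "will receive either a video narrative and standard care or standard care alone". Section 2.4 confirms a single allocation: "Assigning of patients to one of two study arms will take place after the baseline screening". There is no single-viewing arm and no second randomisation.
- **Viewing schedule.** Section 3.1: "The patients will view the video at baseline: T0, 3rd month: T1 and 6th month: T2 immediately after outcome measure assessment".
- **Outcome schedule.** Section 4.1: "The primary outcome measure assessed at T0, T1, T2, T3, and T4 refers to medication understanding and use self-efficacy (MUSE").
- **Analysis.** Section 4.3: "Generalized mixed model analysis is adapted to investigate the variances between groups over time for all outcomes evaluated at the allocated time". No contrast for reinforcement is named.

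**The concern.** The effect of repetition is a comparison at one time point: MUSE after repeated viewings against MUSE after a single viewing. At T2, T3 and T4 the second quantity is never observed, because every video-arm patient is scheduled to have had the repeats by then. The trial will show how the gap between video and control develops. It will not show how much of that development is due to the repeats.

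What is at stake is the interpretation. A gap that widens from T1 to T3 would invite the statement that repetition works, and a flat gap the statement that it adds nothing. Neither follows from the data alone. Section 5 hopes that the results will inform further patient education in stroke care, so a conclusion about repetition could be carried into practice.

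**Working it through.** **Step 1. The plan's own figure.** Section 2.3 sizes a two-group t test "using an alpha of 0.05 and a power of 0.80" for an effect size of 0.4, read here as a mean difference in SD units. Sidedness is not given; two-sided is assumed. The normal approximation is n per arm = 2(1.960 + 0.842)²/0.4² = 98.1, so 99. The t test gives 99.08, so 100. Power at 100 per arm is 0.80 to 0.81. The stated 100 per group is reproduced (a one-sided test would need 78). It is sized for video against no video only.

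**Step 2. Viewings before each assessment.** Each viewing follows that visit's assessment, so the planned counts in the video arm are:

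| Visit | T0 | T1 | T2 | T3 | T4 |
|---|---|---|---|---|---|
| Month | 0 | 3 | 6 | 9 | 12 |
| Viewings completed | 0 | 1 | 2 | 3 | 3 |

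**Step 3. What the arm differences contain.** Let f be the effect of the first viewing at a visit, free to grow or fade, and g the added effect of the repeats. With D the video-minus-control difference:

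- D(T0) = 0, by randomisation
- D(T1) = f(T1)
- D(T2) = f(T2) + g(T2)
- D(T3) = f(T3) + g(T3)
- D(T4) = f(T4) + g(T4)

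The control arm supplies the 5 common visit effects. That leaves 4 informative differences for 4 + 3 = 7 unknowns.

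**Step 4. Rank of the design** (arm-by-visit means):

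| Design | Parameters | Rank | Reinforcement effects estimable |
|---|---|---|---|
| Planned two arms, f free | 5 + 4 + 3 = 12 | 9 | 0 of 3 |
| Planned two arms, f constant T1 to T4 | 5 + 1 + 3 = 9 | 9 | 3 of 3 |
| Hypothetical third arm with one viewing, f free | 12 | 12 | 3 of 3 |

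In the first row, the 5 visit effects and f(T1) are estimable. The third row shows that the missing single-viewing comparator is the cause.

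**Step 5. Size of the ambiguity.** Assume, for illustration only, arm differences of 0.2, 0.3, 0.4, 0.4 SD at T1 to T4. Three accounts give exactly these values:

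| Account | f at T1, T2, T3, T4 | g at T2, T3, T4 |
|---|---|---|
| (a) slow growth, no reinforcement | 0.2, 0.3, 0.4, 0.4 | 0, 0, 0 |
| (b) constant first effect | 0.2, 0.2, 0.2, 0.2 | 0.1, 0.2, 0.2 |
| (c) fading first effect | 0.2, 0.1, 0.05, 0 | 0.2, 0.35, 0.4 |

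Under the constant-effect assumption the estimate of g is D minus D(T1), here 0.1, 0.2, 0.2. It is right under (b), too high under (a) and too low under (c).

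**The case against.** A reader might infer something stronger: that repetition is inseparable from time in every sense and from the first viewing altogether, and that number of viewings and elapsed time are fully confounded. The documents do not support that, for three reasons.

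- Controls are assessed at the same five visits, so the time trend common to both arms can be removed. Only time since the first viewing remains entangled with repetition.
- The T1 assessment precedes the second viewing, so the 3-month effect of one viewing is estimable.
- Viewings and months are not collinear, because T3 to T4 adds time but no viewing. A first-viewing effect growing steadily by δ per visit predicts δ, 2δ, 3δ, 4δ; a lasting gain of δ per viewing predicts δ, 2δ, 3δ, 3δ. These differ at T4. The two explanations coincide only if growth happens to stop by T3 or, more generally, if the first-viewing effect is left free at each visit.

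It can also be said that the sentence in section 2.1 may mean only how the arm difference develops as viewings accumulate, that the trial is labelled exploratory, that no hypothesis or sample size rests on reinforcement, and that an analysis plan not shown may add a contrast. This lowers the stakes. It does not remove the point: the sentence names repetition and says that its impact will be determined, and the obstacle lies in the allocation and viewing schedule given in the article. An analysis plan could only add an assumption. Comparing patients who happened to miss viewings would not be randomised, and section 3.1 has those who miss visits recorded as lost to follow-up and eventually withdrawn.

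**Conclusion.** The point holds in a limited form. The planned design estimates the effect of the three-viewing programme against standard care, and at T1 the 3-month effect of one viewing. It does not identify the increment from repetition at T2, T3 or T4 unless the course of the first viewing's effect is assumed. With that effect left free, 0 of 3 reinforcement effects are estimable, and a larger sample would not change this. With it held constant from T1 to T4, all 3 are estimable, but the article does not state that assumption and the two-arm data cannot test it. The spread of 0 to 0.4 SD at T4 comes from assumed arm differences and is an illustration, not a forecast. The claim that repetition will be determined should be corrected; the primary comparison of video with standard care stands.

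**What to change.** Replace the reinforcement sentence in section 2.1 with text to this effect:

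> The trial estimates the effect of the three-viewing video programme versus standard care. Arm differences at T1, T2, T3 and T4 will be reported as cumulative effects after one, two, three and three viewings. No separate effect of reinforcement will be claimed.

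If an estimate of the increment is still wanted, define it as the arm difference at T2, T3 or T4 minus that at T1. Label it exploratory, and state beside it the assumption that the first viewing's effect is constant from T1 to T4.

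The cost is one sentence and the loss of a claim that the design cannot support. Arms, visits, viewing schedule and sample size stay as they are. Identifying the increment by design would need a randomised single-viewing comparator with its own sample size, since 100 per group covers only the two-arm comparison; the correction proposed here does not require that.
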